### Sample size

The calculation of the sample size is carried out to compare means, with an alpha risk of 0.05 (95% confidence level) and a beta risk of 0.20 (80% power). For an estimated difference in SBP of 5 mmHg and a standard deviation of SBP of 2.5 mmHg, the number of persons necessary is 251 patients per group. Increased by 20% for possible losses, giving a total of 301 patients in each group.

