### Follow-up

Table 4 shows the follow-up plan and patient data collection. Functions of the professionals participating in the study are described in Table 5.

**Table 4 T4:** Follow-up plan and collection of patient data

			
**Enrolment allocation**	**Intervention group:**		
	15 HC selected from those participating in ESCARVAL-risk study.		
	350 patients randomly selected from the total amount of patients with IHD registered in the electronic health records.		
	Patients are enrolled by their primary care physicians. (Inclusion and exclusion criteria).		

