	**Control group:**		
	A random sample of patients (350) with IHD selected from 72 HC electronic records (from ESCARVAL-risk study)		
**Intervention follow-up: 1 year**	Baseline data		
	Personalized follow-up record		
	Starting formative intervention strategy for professionals and patients:		
	**Intervention**	**Patients**	**Professionals**
	**First visit**	Evaluate monitoring of CVRF	Advice online by cardiologist
		Accord control objectives	Monthly updates
		Adherence control	Protocols, guides and bibliography reviews
		Therapeutic education	In-class training course
	**Second visit**	Evaluate monitoring of CVRF	Advice online by cardiologist
		Accord control objectives	Monthly updates
		Adherence control	Protocols, guides and bibliography reviews
		Therapeutic education	In-class training course
	**Third visit**	Evaluate monitoring of CVRF	Advice online by cardiologist
		Accord control objectives	Monthly updates
		Adherence control	Protocols, guides and bibliography reviews
		Therapeutic education	In-class training course
		Number of hospital admissions	
**Outcomes**	Statistical analysis. Loses to follow-up.		
	Presentation of results at participating HC.		
	Final report		

*HC*, Health Center.

**Table 5 T5:** Functions of the professionals participating in the study

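### The printed sample-size inputs (5 mmHg difference, SD 2.5 mmHg) give about 4 to 6 patients per group, not 251, so at least one printed figure is wrong

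*Protocol article*

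**What the plan says.** The Sample size section of the protocol article sets out the whole calculation in three sentences. The type of comparison is given as "The calculation of the sample size is carried out to compare means", with "alpha risk of 0.05 (95% confidence level") and "a beta risk of 0.20 (80% power"). The variable is SBP and the difference to be detected is 5 mmHg. The section then gives "a standard deviation of SBP of 2.5 mmHg, the number of persons necessary is 251 patients per group", followed by the allowance for losses: "Increased by 20% for possible losses, giving a total of 301 patients in each group". It does not state sidedness, a source for the SD, or a design effect.

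Table 4, in the Follow-up section, gives another number. For the intervention group it reads "350 patients randomly selected from the total amount of patients with IHD registered in the electronic health records", and for the control group "A random sample of patients (350) with IHD selected from 72 HC electronic records". Nothing in the text shown links 350 to 301 or 251.

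The Outcome measures section makes hospitalizations the primary outcome and lists blood pressure among the secondary outcomes.

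**The concern.** A difference of 5 mmHg with an SD of 2.5 mmHg is a standardized difference of 2.0. An effect that large needs only a handful of patients per group, so a requirement of 251 cannot come from it. The article prints every input the formula needs, so this is not detail left to a fuller document. It is a complete calculation that does not agree with itself.

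This is the only power statement in the article, and the Discussion rests part of the validity of the results on the calculated sample size. As printed, the 80% power cannot be verified. A reader who took the SD of 2.5 mmHg at face value would conclude that 251 per group can detect about 0.6 mmHg. That would badly mislead anyone interpreting a null SBP result or reusing the SD to plan another trial.

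**Working it through.** **Inputs, all from the Sample size section.** Two independent means; alpha 0.05; power 80%; difference 5 mmHg; SD 2.5 mmHg; equal groups. Sidedness is not stated. Two-sided is assumed from the reference to 95% confidence, and one-sided was also tried.

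**Attempt to reproduce 251.** n per group = 2 × (z₁₋α/₂ + z₁₋β)² × SD² / difference² = 2 × (1.96 + 0.8416)² × 2.5² / 5² = 3.92, so 4 per group.

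Exact two-sided t-test at a standardized difference of 2.0: power is 79.1% with 5 per group and 87.6% with 6, so 6 are needed.

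Ratio of the stated figure to these results: 251/6 = 42 and 251/4 = 63.

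**Other readings tried.**

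| Reading | n per group |
|---|---|
| One-sided, 80% power | 4 |
| Two-sided, 90% power | 6 (t-test 7) |
| Two-sided, 95% power | 7 |
| 2.5 read as a variance | 2 |
| Figures swapped (difference 2.5, SD 5) | 63 |
| Lost decimal point (difference 5, SD 25) | 393 |

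Unequal allocation (ratios 0.5 to 3) gives 3 to 6. No reading comes near 251. With the printed inputs, power at 251 per group is practically 100%.

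**What 251 does imply.** Solving the two-sided formula for the standardized difference: √(2/251) × (1.96 + 0.8416) = 0.250. Two simple pairs of inputs give this:

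- difference 5 mmHg: SD = 19.99 mmHg
- difference 2.5 mmHg: SD = 10.00 mmHg

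Either pair gives an unrounded n of 2 × (1.96 + 0.8416)² / 0.25² = 251.2. If the SD really were 2.5 mmHg, the difference detectable with 251 per group would be 0.25 × 2.5 = 0.63 mmHg.

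**Losses.** 251 × 1.20 = 301.2, which reproduces the stated 301. If 20% of 301 were lost, 301 × 0.80 = 240.8, about 241, would remain. Keeping 251 after a 20% loss needs 251/0.80 = 313.75, so 314.

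**Table 4.** 350/1.20 = 291.7 and 350 × 0.80 = 280, so 350 follows from neither 251 nor 301.

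**Power of the two-sided t-test at a standardized difference of 0.25, ignoring clustering by health center.**

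| Analysed per group | Power |
|---|---|
| 241 | 78.2% |
| 251 | 79.8% |
| 280 | 84.0% |

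**The case against.** The mismatch between the printed inputs and 251 has no good defence. The figures stand in running text, so table breakage or redaction does not explain them, and no alternative reading recovers the number. The case on the other side concerns how much more may be concluded, and most of it stands.

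- **That the SD is misprinted by a factor of eight.** A reader might infer this because 20 mmHg needs only one changed input. But 251 fixes only the ratio of difference to SD, and 2.5 mmHg with an SD of 10 mmHg fits equally well. The document does not say which figure is wrong.
- **That the loss allowance is an arithmetic error.** The text announces a 20% increase and carries it out correctly. It does not state an expected loss rate of 20%. The shortfall appears only if 20% are in fact lost, and it is then small: 78.2% power against 79.8%.
- **That 301 and 350 contradict each other.** Table 4 describes 350 patients selected from the records. Enrolment by the physicians, subject to eligibility criteria, comes after that, and the Randomization section says that participation is offered to patients already selected. So 350 may be the number sampled before eligibility and consent, and 301 the number needed. The flow diagram, which might settle this, is not shown. The text does not state this reading either, so a request for clarification remains fair.
- **That Table 4 already covers any shortfall, with 84% power.** This holds only if all 350 enrol. If 350 is the number approached, reaching 314 needs 314/350 = 90% uptake.

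**Conclusion.** The sample-size statement is wrong as written. Its own inputs require 4 patients per group (6 by the exact two-sided t-test), against a stated 251, so at least one input or the group size is incorrect. This conclusion needs no outside figure and does not depend on sidedness.

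What the calculation was meant to be is an inference. Under a two-sided test it used a standardized difference of 0.25, most simply 5 mmHg with an SD near 20 mmHg. The powers of 78%, 80% and 84% rest on that value and on ignoring clustering. They apply to SBP only and say nothing about power for hospitalizations.

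The loss allowance and the unexplained 350 are minor points of clarity, not proven errors.

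**What to change.** 1. Restate the difference and SD actually used, with the source of the SD and the sidedness of the test, so that they reproduce 251. If they do not, correct the 251.
2. Say in the same paragraph that the calculation is for SBP, a secondary outcome, and that it does not give the power for the primary outcome.
3. If a 20% loss is expected, either report the power with about 241 analysed (about 78% at a standardized difference of 0.25) or state that 314 per group would be needed to keep 251.
4. State in Table 4 whether 350 is the number selected before consent or the enrolment target, and reconcile it with 301. Quote a power for 350 only if it is the enrolled number: about 84% with 280 analysed, at a standardized difference of 0.25 and ignoring clustering.

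The cost is a few corrected sentences. Whether more patients would have to be approached depends on the inputs actually used and on what 350 means, so that should not be promised either way.

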### Randomization, allocation and implementation

Valencia is a Mediterranean Spanish Region with 5 million inhabitants. In 2007, 800 primary care physicians and nurses started the ESCARVAL primary prevention cohort study [20]. 72 Health centers (HC) participated including 50000 patients.

For the intervention group in the PROPRESE study 15 HC are selected from those participating in ESCARVAL. Once the center agreed to participate patients are randomly selected from the total amount of patients with IHD registered in the electronic health records.

For the control group a random sample of patients with IHD is selected from all 72 HC electronic records.

Patients are enrolled by their primary care physicians who will offer to participate to the randomly selected patient.

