### Participants

Setting: Primary Health Care. Valencian Community (Spain).

15 Health centers: Alicante-Cabo-Huertas, Alicante-Campello, Alicante-Plà Hospital, Castellón-Dolores-Cano-Royo-Villareal, Castellón-La-Bobila-Villareal, Castellón-Cariñena-Villareal, Castellón-Nules, Castellón-Vall d’Uxo I and II; Valencia-S Pau, Valencia-R-Argentina, Valencia-Benimaclet and Valencia-Serreria-II.

Inclusion criteria: patients with a diagnosis of IHD of any site (ICD-10 codes from 410 to 414 inclusive); age from 30 to 80 years; signed written informed consent. Exclusion criteria: lack of consent; immobilized patients; patients with serious health problems or with a low life expectancy.

Data are collected from electronic health record system.

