a) Formative. Four face-to-face workshops (every 3 months); monthly clinical session on cardiovascular disease; online tutorials with the cardiology service to solve any doubts. Face-to-face tutorials with a team, reference doctor/nurse, in each health center.

a) Strategies to avoid clinical inertia: carry out therapeutic changes if there is poor control before 3 months.

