### Blinding

Blinding is not possible as the intervention is a multifactorial approach. That’s why the control group is selected after the intervention is made but for the same period of time.

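### The control sample is drawn from all 72 centers, including the 15 intervention centers, so about a fifth of controls may come from centers where staff were trained, which can dilute the contrast

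*Protocol article*

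**What the plan says.** Under Randomization, allocation and implementation, the article describes ESCARVAL: "72 Health centers (HC) participated including 50000 patients". The intervention centers come from that set: "For the intervention group in the PROPRESE study 15 HC are selected from those participating in ESCARVAL". The control rule is "For the control group a random sample of patients with IHD is selected from all 72 HC electronic records". The abstract gives the same frame, and Table 4 repeats it with a number: "A random sample of patients (350) with IHD selected from 72 HC electronic records (from ESCARVAL-risk study".

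The intervention has a patient part and a professional part. The professional part comprises quarterly workshops, monthly clinical sessions, online cardiology tutorials, measures against clinical inertia and, under Interventions, "Face-to-face tutorials with a team, reference doctor/nurse, in each health center". The Blinding section sets the timing: "the control group is selected after the intervention is made but for the same period of time".

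The eligibility rules under Participants end with "Exclusion criteria: lack of consent; immobilized patients; patients with serious health problems or with a low life expectancy". They do not mention belonging to an intervention center or already being in the intervention group.

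**The concern.** The 15 intervention centers lie inside the control frame. A control drawn from one of them was cared for, over the same year, at a center where staff were attending the training. Training acts on doctors and nurses, who also see IHD patients outside the intervention group. Such a control may therefore receive part of what is being tested.

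Wherever that part is beneficial, the comparison is pulled toward no difference. A larger sample can recover power, but it does not remove the bias in the estimate. A null or small result could then mean either a weak intervention or a contaminated comparator. This matters here because the Background already reports disappointing results from similar programs.

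The rule as stated also does not prevent an enrolled intervention patient from being drawn again as a control.

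**Working it through.** **1. Is the overlap real?** There are 72 ESCARVAL centers, the 15 intervention centers are chosen from them, and the control frame is all 72. The frame therefore contains the 15. The abstract, the allocation section and Table 4 agree, and the eligibility criteria do not undo it.

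**2. Expected share of controls.** Assume equal IHD lists per center and simple random sampling; the article gives no list sizes.

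- 15/72 = 0.208, or 21%.
- 301 × 15/72 = 62.7, about 63 controls. 350 × 15/72 = 72.9, about 73 controls.
- Participants appears to name only 13 centers (counting Vall d'Uxo I and II as two). 13/72 = 18%, still about a fifth.

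**3. The plan's own sample size.** The inputs under Sample size are a difference of 5 mmHg, SD 2.5 mmHg, alpha 0.05 (taken as two-sided) and power 80%, with a stated result of 251 per group.

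- n = 2 × [SD × (1.960 + 0.842) / difference]².
- With SD 2.5: 2 × (2.5 × 2.802 / 5)² = 3.9, so 4 per group. The stated 251 is not reproduced.
- Solving for the SD: 5 × √(251/2) / 2.802 = 19.99. With SD 20 the formula gives 251.2.

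The illustration below therefore uses SD 20 mmHg. This is an assumption inferred from the 251, not a figure in the article.

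**4. Dilution.** Let c = 15/72 be the share of controls from intervention centers. Let s be the spill-over, meaning the fraction of the full effect that those controls receive.

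- Observed difference = 5 × (1 − c × s).
- Power = Φ(observed difference / SE − 1.960), with SE = 20 × √(2/251) = 1.785.
- The last column is the n per group needed for 80% power.

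| Spill-over s | Observed difference (mmHg) | Power at 251 per group | n per group for 80% |
|---|---|---|---|
| 0% | 5.00 | 80% | 252 |
| 25% | 4.74 | 76% | 280 |
| 50% | 4.48 | 71% | 313 |
| 100% | 3.96 | 60% | 401 |

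**5. Sensitivity to the share.** If unequal center sizes put the share anywhere from 10% to 30%, full spill-over gives 4.5 to 3.5 mmHg and power of 71% to 50%. Smaller spill-over gives proportionally less dilution.

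**6. Primary outcome.** The same factor, 1 − c × s, applies to a difference in mean hospitalizations: 0.95, 0.90 and 0.79 at 25%, 50% and 100% spill-over. The article gives no expected admission rate or target difference, so no power figure can be attached.

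**The case against.** The overlap itself is hard to dispute. The case against concerns how much can be built on it, and several parts of that case stand.

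- **A reader might infer that a fifth of controls are treated by trained teams and get the whole effect.** The article does not support this. It does not say what share of staff in each center takes part. The therapeutic education, personalized record, agreed objectives and planned visits belong to enrolled patients. Full spill-over is an upper bound, and the 60% power figure should not be the headline.
- **The power figures depend on an SD that the article does not give.** With the printed 2.5 mmHg, power at 251 per group would stay at essentially 100% in every row. The figures also concern blood pressure, a secondary outcome. They illustrate the mechanism only.
- **A reader might infer that every comparison is biased toward no effect.** That holds only for outcomes on which training helps patients who were not enrolled. The article does not show this for visit counts, diet, exercise or smoking.
- **A reader might count it as a further harm that one center supplies patients to both arms.** It is not one. Shared centers tend to make the arm means covary positively, which lowers the variance of their difference. The problem is contamination.
- **Redrawing of enrolled patients may be prevented in practice.** The text does not state a safeguard, and the flow diagram is not available to check. This is something the rule permits; nothing shows that it happens.

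The strongest remaining argument is that restricting controls to other centers confounds center with arm. The cost is real but limited. About four fifths of controls are already expected from other centers, the plan describes no within-center comparison, and intervention centers are chosen and then agree to take part, without stated randomization between arms. Keeping the 15 centers in the frame does not cure that.

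**Conclusion.** The point holds and should be fixed. The stated sampling rule places patients of intervention centers in the comparator during the intervention year. This is a fault in a rule that the article gives explicitly in three places, so it is not detail left to a fuller document.

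The expected share is about a fifth, on the assumption of equal IHD lists. The resulting bias is of uncertain size and runs from none, if training does not reach other patients, to the 21% bound for that share. Moderate spill-over of 25% to 50% means a 5% to 10% loss of the contrast. The direction, toward no difference, depends on training benefiting patients who were not enrolled. The blood pressure power figures also rest on the assumed SD of 20 mmHg.

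The documents do not support calling the trial uninformative on this ground alone. The lack of randomization between arms is a separate and larger matter.

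**What to change.** Change the sampling rule so that controls are drawn only from ESCARVAL centers that are not intervention centers (72 − 15 = 57), and exclude anyone enrolled in the intervention group. Because controls are selected last, this need not disturb the intervention arm. The article gives no IHD counts, so the sponsor should confirm that the remaining centers can supply the sample; 350 controls would be about 6 per center (350/57 = 6.1).

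If controls have already been drawn, exclude those from the 15 centers in the primary analysis and report the comparison with all 72 centers as a sensitivity analysis. On the equal-list assumption this leaves about 277 of 350 controls, or 238 of 301. The latter is below 251 even before losses.

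The cost in interpretation is that arm and center become fully separated. The report should acknowledge that participating centers may differ from the others, and the multivariate analysis should adjust for baseline data. Adjustment reduces this problem but does not replace randomization.

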### Outcome measures

Primary outcome measure: number of hospitalizations/cause. It is measured at the beginning and end of the study.

Secondary outcomes:

a) Level of control of CVRF: Blood pressure, LDL cholesterol, body mass index, basal blood glucose, HbA1c, therapeutic compliance (pill count), smoking. They are measured at each visit.

b) Healthy life habits: Exercise, mediterranean diet. They are measured at each visit.

c) Management: Number of annual primary care visits. It is measured at the end of the study.

To enhance the quality of measurements a training program is performed and there was one assessor for every three health centers.

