Some multifactorial interventions have been published specially based on nurse work [26] but no very good results have been obtained. Our study has some different aspects that can be mentioned: we use an unique electronic health record for primary and secondary care improving communication between professionals, we implement CCM strategies involving patients with self-care, sharing decisions about the level of control to be reached and objective based treatments, involving all primary care team (physicians and nurses) and cardiologists.

In conclusion, this study will provide information about the efficacy of a patient-centered intervention based on the CCM. Actions will be centered on identifying the higher-risk patients, such as those in secondary prevention; on greater patient information and capacity, favoring autonomy; on shared decision making to establish and reach the control objectives; and an individualized programming of appointments, relying for all this on the teamwork of primary care nurses and physicians under the supervision of the reference cardiology service.

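### Intervention patients come from 15 selected centers and controls from a simple random draw over all 72, so the mix of areas can differ by arm and confound the comparison of hospitalizations

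*Protocol article*

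**What the plan says.** All references are to the protocol article.

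- **Intervention arm** (Randomization, allocation and implementation): "For the intervention group in the PROPRESE study 15 HC are selected from those participating in ESCARVAL". Patients are then sampled at random within the centers that agree to take part.
- **Control arm** (same section): "For the control group a random sample of patients with IHD is selected from all 72 HC electronic records". The abstract and Table 4 give the same rule, and none of the three places mentions area, hospital, age or sex.
- **Location of intervention centers** (Participants): three entries in Alicante, four in Valencia and six in Castellón, the last being "Castellón-Dolores-Cano-Royo-Villareal, Castellón-La-Bobila-Villareal, Castellón-Cariñena-Villareal, Castellón-Nules, Castellón-Vall d’Uxo I and II". That makes 13 names against the 15 stated.
- **Primary outcome** (Outcome measures): "Primary outcome measure: number of hospitalizations/cause", recorded at the start and end of the study.
- **Timing and source**: the Blinding section says "the control group is selected after the intervention is made but for the same period of time", and Participants says "Data are collected from electronic health record system".
- **Analysis** (Statistical analysis): chi-square, t test and ANOVA, followed by a multivariate analysis whose covariates are not named.

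**The concern.** Random sampling within each arm's frame is not random allocation between arms. It makes each sample representative of its own frame, but the frames differ: one is a set of chosen centers concentrated in a few localities, the other is the whole ESCARVAL network. Only the sampling rule or the analysis can then balance geography, and the stated sampling rule does not.

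This matters for the chosen outcome. Admission can plausibly vary with local hospital practice and with the age and sex mix of the area. The intervention also runs partly through cardiology, with primary care teams working "under the supervision of the reference cardiology service". If areas differ in admission rate for reasons unrelated to the intervention, part of that difference is carried into the primary comparison, and it could pass for either benefit or harm.

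The Discussion rests validity on how representative the sample is. For this comparison the useful control group is one that resembles the intervention patients in everything but the intervention, which is a different target from representing all 72 centers.

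**Working it through.** The article gives no figure for this bias, so there is none to reproduce. What follows is an illustration on stated assumptions.

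**Inputs from the article.** Named intervention centers: Alicante 3, Castellón 6 (counting Vall d'Uxo I and II as two), Valencia 4, total 13. Shares: 3/13 = 23%, 6/13 = 46%, 4/13 = 31%. Control frame: 72 centers, which include the 15. Planned size: 301 per group (Sample size).

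**Assumptions.** Centers contribute equally. Castellón holds a share *s* of the control sample, 0.10 to 0.30. The Castellón admission rate differs from elsewhere by a fraction *k* = ±0.25. The intervention has no effect.

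**Spurious rate ratio.** With *p* the Castellón share in the intervention arm, RR = (1 + k·p) / (1 + k·s).

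| k | p | s = 0.10 | s = 0.30 |
|---|---|---|---|
| +0.25 | 6/13 | 1.1154/1.025 = 1.088 | 1.1154/1.075 = 1.038 |
| −0.25 | 6/13 | 0.8846/0.975 = 0.907 | 0.8846/0.925 = 0.956 |
| +0.25 | 6/15 (both unnamed centers elsewhere) | 1.1000/1.025 = 1.073 | 1.1000/1.075 = 1.023 |
| +0.25 | 8/15 (both unnamed centers in Castellón) | 1.1333/1.025 = 1.106 | 1.1333/1.075 = 1.054 |

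On the named centers the ratio is about 1.04-1.09, or 0.91-0.96 if Castellón admits less. Uncertainty over the two unnamed centers widens the upper case to about 1.02-1.11.

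**Absolute scale, wider assumptions.** Treat the outcome as any admission within 12 months, with risk 10-20% outside Castellón, Castellón at 0.6 to 1.5 times that, and a control share of 10-33%. The spurious difference then runs from 0 to about 3.6 percentage points in size. The extreme case has base risk 0.20, ratio 1.5 and s = 0.10:

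- intervention risk 0.20 × (1 + 0.5 × 0.4615) = 0.246;
- control risk 0.20 × (1 + 0.5 × 0.10) = 0.210;
- difference 0.036.

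At 301 per group a two-sided 0.05 test would reject in about 18.5% of trials in that case. With a 25% higher Castellón rate and s = 0.10, the figure is 6.5% at a base risk of 10% and 8.4% at 20%. If admission risk does not vary by area, it stays at 5%.

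**Overlap of the frames.** With equal center sizes, 15/72 = 21% of controls would come from intervention centers (about 73 of 350, or 63 of 301).

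**Effect of stratifying without excluding intervention centers.** Count the 13 named centers and pool the areas outside Castellón.

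- s = 0.10: Castellón has 7.2 centers, of which 6 are intervention centers. The exposed share of controls is 0.4615 × 6/7.2 + 0.5385 × 7/64.8 = 0.385 + 0.058 = 44%, against 13/72 = 18% under the current draw.
- s = 0.30: 0.4615 × 6/21.6 + 0.5385 × 7/50.4 = 0.128 + 0.075 = 20%, against the same 18%.

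A stratified draw that keeps the intervention centers could therefore put many more exposed patients among the controls.

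**The case against.** Several points on the other side carry weight.

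- **The arms are not drawn from separate catchments.** A reader might infer that admissions are compared across different hospital catchments. The article does not support that: the 15 centers belong to the 72, so only the mix differs. It gives no catchments, no locations for the other centers and no admission rates by area. This stands.
- **The analysis may absorb part of the difference.** Baseline hospitalizations are recorded and a multivariate analysis is planned. An article need not list covariates, so their absence is not itself a fault. Prior admissions could take up some of any stable area difference, though nothing stated ensures that they or area will be in the model.
- **Matching on area can do harm.** The intervention trains professionals and reorganizes whole teams, so controls from those centers may be partly exposed. The overlap arithmetic is right, and it rules out any stratified draw that keeps the intervention centers. Excluding them has its own limit: at s = 0.10 only about 7.2 − 6 = 1.2 Castellón centers would remain.
- **The change is not free.** Because controls are taken later from records, one might infer that a stratified draw costs nothing. The Informed consent section requires a signed form from every patient, so on the text this is more than a records query. That burden falls on any control sample, however, so the extra cost of stratifying is small.
- **It is a secondary symptom.** The larger weakness is that centers are selected and agree to take part. That stands too, but the area mix is a separable part of it that can be reduced.

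**Conclusion.** The point holds in limited form. The article fixes a plain random control draw in three consistent places and an intervention arm from selected centers, so the mix of areas can differ by arm on an outcome that may depend on area. An imbalance in age or sex is possible, but nothing in the article shows one.

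Neither the existence, the size nor the direction of a bias is established. The ratios of about 1.04-1.09, or 0.91-0.96 in the other direction, rest on an assumed 25% rate difference, an assumed 10-30% Castellón share, equal center sizes and the 13 named centers. They show that a modest area difference would be enough to matter, not that one exists. The change is worth making because it is cheap relative to the ambiguity it removes, but it leaves the non-random selection of intervention centers in place.

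**What to change.** 1. In the abstract's Methods/design, in Randomization, allocation and implementation, and in Table 4, state that controls are drawn from the ESCARVAL centers not in the intervention arm. Sample them at random within strata, in proportion to the enrolled intervention patients' distribution of province, age band and sex. Use hospital area in place of province where enough non-intervention centers exist.
2. In Statistical analysis, name province or area, age, sex and baseline hospitalizations as terms in the multivariate analysis. Rely on this adjustment where an area has too few non-intervention centers to match, and say so, because the estimate for that area then leans on few controls.

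Cost: a more detailed sampling query and a few model terms, with consent required as for any control sample. Controls would no longer represent all 72 centers, and some areas may have few eligible control centers.
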